## Abstract

**Background:**

Despite the availability of effective treatments for bulimia nervosa (BN), a number of barriers to accessibility exist. Examples include access to trained clinicians, the expense of treatment, geographical limitations, and personal limitations such as stigma regarding help seeking. Self-help interventions, delivered via a digital platform, have the potential to overcome treatment gaps by providing patients with standardised, evidence-based treatments that are easily accessible, cost-effective, and require minimal clinician support. Equally, it is important to examine the shortcomings of digital interventions when compared to traditional to face-to-face delivery (e.g., high dropout rates) in order to maximise the therapeutic effectiveness of online, self-help interventions.

**Methods:**

A three-arm, multisite randomised controlled trial will be conducted in Australia examining the effectiveness and cost-effectiveness of a newly developed online self-help intervention, *Binge Eating eTherapy (BEeT),* in a sample of patients with full or sub-threshold BN. The BEeT program consists of 10, multimedia sessions delivering the core components of cognitive behaviour therapy. Eligible participants will be randomised to one of three groups: independent completion of BEeT as a purely self-help program, completion of BEeT alongside clinician support (in the form of weekly telemedicine sessions), or waitlist control. Assessments will take place at baseline, weekly, post-intervention, and three-month follow up. The primary outcome is frequency of objective binge episodes. Secondary outcomes include frequency of other core eating disorder behavioural symptoms and beliefs, psychological distress, and quality of life. Statistical analyses will examine treatment effectiveness, feasibility, acceptability and cost effectiveness.

**Discussion:**

There is limited capacity within the mental health workforce in Australia to meet the demand of people seeking treatment for eating disorders. This imbalance has only worsened following outbreak of the COVID-19 pandemic. Further research is required into innovative digital modes of treatment delivery with the capacity to service mental health needs in an accessible and affordable manner. Self-help programs may also appeal to individuals who are more reluctant to engage in traditional face-to-face treatment formats. This study will provide rigorous evidence on how to diversify treatment options for individuals with BN, ensuring more people with the illness can access evidence-based treatment.

The study has been registered with the Australia New Zealand Clinical Trials Registry (ANZCTR Registration Number: ACTRN12619000123145p). Registered 22 January 2019, https://www.australianclinicaltrials.gov.au/anzctr/trial/ACTRN12619000123145.

## Introduction

Bulimia nervosa (BN) is an eating disorder (ED) characterised by recurrent objective binge episodes followed by behaviours intended to compensate for the food eaten during the binge [1]. Binge episodes must involve the consumption of an objectively large amount of food and be accompanied by a sense of lack of control [1]. BN is one of the most common types of EDs globally [2]. According to the Global Burden of Disease Study, the global prevalence rates of BN in 2019 was estimated to be 176.2 per 100,000 people [2]. Epidemiological research conducted on an Australian sample from 1998 to 2008 has identified an upward trend in core symptoms BN including objective binge episodes and extreme dieting [3]. These findings are concerning given the significant physical and psychological impairments imposed by BN [4]. Individuals with BN have been found to report greater functional impairment, higher emotional distress, and lower quality of life than their age-matched peers without the illness [5, 6]. Additionally, significant medical complications are often incurred by individuals with BN as well as economic costs as a result of lower labour force participation, greater absenteeism, and higher health-care costs [2, 7, 8]. The impacts of the illness are only worsened by personal barriers of shame and stigma associated with disordered eating behaviours, which function to discourage help seeking and result in worsening of untreated symptoms [9]. Recent research has identified an average delay of 8.4 years between the onset of BN symptoms and the first instance of help seeking behaviours, with stigma reported as the most impactful barrier [10].

Individual psychological therapy is recognised as the first-line treatment for adults with BN [11], with cognitive behavioural therapy (CBT) having the strongest evidence base of all therapeutic modalities [12–14]. Unfortunately, on average only 23.2% of individuals with an ED access an evidence-based treatment [15]. Limited availability of trained clinicians and poor scalability of therapist-led CBT have been identified as contributors to the poor translation of evidence-based research to real-world populations [16]. The capacity of clinical services to meet the demand of BN patients is often limited by the structure of therapist-led CBT, with most evidence-based treatments stipulating 20 hours of face-to-face therapist contact across a 20-week period [17, 18]. Although there is emerging evidence to suggest ten-session therapist-led CBT may produce  similar clinical outcomes for BN [19], the predicament of limited treatment accessibility remains for those residing in rural and remote areas with very few ED trained clinicians operating outside of metropolitan regions of Australia [20]. Given the demands on public health resources, those who are forced to seek treatment within the private sector are faced with a significant financial expense [21]. There are also concerns regarding the quality of CBT being delivered in the community with studies reporting that as few as 6% of clinicians adhere to evidence-based manuals [22].

Greater attention must be directed towards adapting evidence-based treatments to fit within more time- and cost-efficient models of healthcare delivery, thereby improving accessibility and fidelity within resource constraints. As part of a stepped care model, lower intensity treatments, such as online self-help programs, can be offered to those with less severe clinical presentations in order to prioritise specialist therapeutic skill for patients with greater symptom complexity. Technology-based interventions allow for numerous patients to simultaneously engage with standardised, evidence-based treatments at any time and location that best suits them [16, 23]. The anonymity of digital interventions may assist with the shame and secrecy experienced in relation to bulimic behaviours and the seeking of treatment [24]. Importantly, the recent COVID-19 pandemic has emphasised the need for a technology revolution in the mental health care system [25–30]. Fortunately, digital platforms have allowed mental health services to meet the needs of patients in lieu of in-person contact, highlighting the convenience and flexibility of online treatments and their capacity to overcome the shortcomings of traditional treatment delivery in the current pandemic situation [26, 27, 31, 32].

Several systematic reviews have concluded that digital self-help interventions are effective in reducing eating disorder behaviours [33–40]. There is evidence to also suggest that the treatment outcomes of self-help interventions are significantly enhanced by the addition of low-intensity support from a clinician, such as a fortnightly, check-in email or phone call [12, 39, 41–43]. Supported self-help interventions only demand one-fifth of the therapist contact hours required for a complete CBT course, meaning they can be delivered in settings with low resources and capacity limits [42]. The provision of clinician support as an adjunct to self-help programs has been suggested as a viable solution to one of the most powerful critiques of digital interventions, that being the high rates of non-adherence [37, 38]. Internet-delivered CBT has the highest dropout rates of all ED treatments, ranging up to 47.2% [44]. Given the potential impact of non-adherence upon the therapeutic outcomes for patients, several reviews have highlighted the need for ongoing development and examination of novel digital treatments, with the aim of reducing the discrepancy in adherence between online platforms and more traditional modes of face-to-face treatment delivery [35, 37, 38].

Two large published studies provide evidence for the use of online CBT-based, self-help programs for individuals with BN. As part of a randomised controlled trial (RCT) conducted by Sánchez-Ortiz et al. [45] significant improvements were reported in a sample of 75 patients with full or subthreshold BN following completion of an eight-session online CBT-based program. Abstinence rates were comparable to those of patients receiving a manual-based CBT self-help intervention and face-to-face CBT program [46, 47]. Similarly, Pretorius et al. [48] observed significant reductions in BN symptomology in response to an online CBT program, supplemented with email support from a clinician and peer support via message boards, which were maintained at six-month follow up. An abridged version of BEeT has also been successfully piloted proving its acceptability, feasibility, and effectiveness in reducing core symptoms of BN [49].

Despite the documented effectiveness of online therapies for ED, the availability and uptake of evidence-based digital interventions in the public has been minimal [50]. Very few of the digital interventions examined in preceding clinical trials uphold the technological sophistication required to support user engagement. For example, very few are available as a smartphone application or employ interactive and personalised functions [35]. Further, the vast majority of ED smartphone applications available in the commercial marketplace have not been developed or evaluated by clinical researchers and provide advice that is not informed by evidence-based approaches [51]. Additionally, to our knowledge none of the current online therapies for EDs are available in Australia, with all programs having been developed and evaluated in the USA, UK, and European countries [35].  Consequently, the pilot study of BEeT is the only known evidence which supports the effectiveness of these technologies within the Australian population [49]. Considering the increasing demand for by-distance treatments in the aftermath of COVID-19, and in order to ensure evidence-based treatments are developed in a timely manner, these questions warrant examination. The Binge Eating eTherapy (BEeT) program was developed to address the need for online CBT-based, self-help programs for BN in Australia and to meet the demand for online therapies with up-to-date digital features which can be safely accessed by the patient themselves.

### Study objectives

This randomized controlled trial will compare three study conditions: (1) independent completion of BEeT as a pure self-help program; (2) completion of BEeT alongside 30-min, weekly clinician support; and (3) waitlist control condition (WLC).

The aims of this current trial are to:Investigate the effectiveness of clinician-supported BEeT compared to pure self-help BEeT and WLC in bringing about significant symptom reduction in individuals with BN or subthreshold BN;Examine site-specific outcomes of treatment implementation of clinician-supported BEeT as a low-intensity, eating disorder treatment intervention within the NSW health system; andDetermine the cost-effectiveness of WLC as compared to both pure self-help BEeT and clinician-supported BEeT.

## Methods

The present study protocol is reported according to the SPIRIT checklist [52].

### Trial design and setting

This study is a multisite, three-arm randomized controlled trial inclusive of two active interventions and a WLC. Participants will be recruited from the general community in Australia via advertisements on health websites and social media, referrals made from health professionals, and paper advertisements in mental health and medical clinics. If considered eligible following a screening call, the participant will be instructed to complete a standardised medical assessment with their general practitioner (GP) prior to entry to the study. After providing written informed consent, participants will be randomised to either the WLC condition or one of the intervention conditions, including pure self-help BEeT or clinician-supported BEeT. The intervention is entirely via digital modalities, including (1) *online eTherapy platform* and (2) *secure videoconferencing platform* (only for participants receiving clinician-supported BEeT). Participants randomised to the clinician-supported BEeT condition will engage in telemedicine sessions delivered by clinicians based at one of the following sites: specialist eating disorder outpatient clinic, adult community mental health team, university-based research team, and youth mental health clinic (headspace). All sites are based within New South Wales, Australia. See “Appendix A” for a list of study sites. Participants will be assessed at baseline (T0), weekly, post-intervention (T1: 12 weeks), and at 3-month follow-up (T2). The study commenced in May 2020. The study protocol has been approved by a Human Research Ethics Review Board (HREC #X18-0486). See Fig. 1 for an overview of the study process.

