#### Pure self-help BEeT

Participants allocated to the pure self-help BEeT treatment group will be given access to BEeT as described following after their baseline assessment.

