## Outcomes

Data will be collected via online self-report assessments. Table 2 provides an overview of assessment points and outcome measures.

**Table 2 Tab3:** Schedule of enrolment, interventions, and assessments according to SPIRIT

	TIMEPOINT**	STUDY PERIOD						
		Enrolment	Allocation	Post-allocation				
		− T_1_	0	T_0_	Weekly monitoring	T_1_	T_2_	T_3_
**Enrolment**	Eligibility screen	X						
	GP Clearance	X						
	Informed consent	X						
	Allocation		X					
**Interventions**	Clinician-supported BEeT							
	Pure self-help BEeT							
	WLC							
**Assessments**	Demographics			X				
	General mental health			X				
	Self-harm and suicidality risk assessment			X	X	X	X	X
	Eating disorder examination questionnaire (EDE-Q)			X		X	X	X
	Eating disorder examination questionnaire-short (EDE-QS)				X			
	Kessler psychological distress scale (K10)			X	X	X	X	X
	Eating disorder quality of life questionnaire (EDQOL)			X		X	X	X
	Three-factor eating questionnaire (TFEQ)			X		X	X	X
	Young schema questionnaire			X		X	X	X
	Body mass index (BMI)			X	X^1^	X	X	X
	European quality of life-5 dimensions-5 levels (ED-5D-5L)			X		X	X	X
	Evaluation of external health services utilised			X		X	X	X
	Implementation surveys					X		
	Working alliance inventory-short revised (WAI-SR)^2^					X		
	Working alliance inventory for online interventions-short form (WAI-TECH-SF)					X		

**T_0_ = baseline assessment, T_1_ = 12 week assessment (post-intervention), T_3_ = 24 week assessment (3 month follow up), T_3_ = 36 week assessment (for WLC only)

^1^BMI measured in fourth week of participation. Also measured weekly from fifth to tenth week for participants where rapid weight loss is indicated

^2^Only administered to clinician-supported BEeT participants

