### Randomisation

Randomisation will be performed independently by the National Health and Medical Research Council Clinical Trials Centre, Sydney Australia (NHMRC CTC). The allocation sequence is a permuted block list consisting of blocks randomly varying between size 6 and 9. The study group allocation will be revealed to the researcher via the NHMRC CTC telephone randomisation service. No stratification factors  will be used.

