### Blinding

It is not possible to blind participants in this trial given that the difference between the two interventions and the waitlist groups can be detected easily. Blinding of outcome assessors is not applicable given all assessments consist of self-report measures. Data analysts will be blinded to the group allocation of participants.

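### Table 2 schedules the self-reported baseline (T0) after allocation, and nothing visible says the arm is withheld until T0 is submitted, so the baseline of the primary change score is open to allocation-aware reporting

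*Protocol article*

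**What the plan says.** All references are to the protocol article.

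- *Trial design and setting*: "After providing written informed consent, participants will be randomised to either the WLC condition or one of the intervention conditions". No baseline assessment is named between consent and randomisation.
- *Outcomes*, Table 2: the columns run from enrolment, to allocation at time 0, to a block headed "Post-allocation" that opens with T0. The footnote defines "T_0_ = baseline assessment". Screening, GP clearance and consent are marked at enrolment. The EDE-Q is first marked at T0.
- *Pure self-help BEeT*: participants allocated to this arm "will be given access to BEeT as described following after their baseline assessment".
- *Blinding*: "It is not possible to blind participants in this trial", and "all assessments consist of self-report measures".
- *Randomisation*: "The study group allocation will be revealed to the researcher via the NHMRC CTC telephone randomisation service". When the participant is told is not stated.
- *Primary outcome* and *Statistical methods*: the outcome is the EDE-Q count of objective binge episodes over the preceding 28 days, analysed as change. The covariates are baseline age, illness severity and length of illness.

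**The concern.** A baseline should be fixed before anything about the allocation can influence it. Here the instrument that supplies the starting value of the primary outcome is scheduled after allocation, and it is a recalled count reported by a participant who cannot be blinded. Someone who knows they have been given treatment, or put on the waitlist, may report the past 28 days differently. The primary outcome is change, so any difference between arms in T0 reporting enters the treatment contrast directly. Blinding the data analysts does not protect a report that has already been given.

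There is a second consequence. A participant who leaves after allocation but before T0 belongs to the intention-to-treat population, yet has no scheduled baseline EDE-Q.

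**Working it through.** **Step 1: the order of events.** The sources side by side:

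| Source | Order it gives |
|---|---|
| *Trial design and setting* | consent, then randomisation; T0 not placed |
| Table 2 | consent at enrolment, allocation at time 0, T0 after allocation |
| *Pure self-help BEeT* | access after baseline, for participants described as allocated |

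Table 2 decides the point. The two text passages fit it but would not establish it alone. No visible passage puts T0 before allocation, and none schedules a pre-allocation EDE-Q. The screening call covers eligibility and is not a scheduled EDE-Q.

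**Step 2: how a T0 shift reaches the estimate.** For each arm, change = T1 − T0. If knowing the arm moves mean reported T0 in one arm by d and leaves T1 alone, that arm's mean change moves by −d. The between-arm contrast is therefore biased by d in absolute size. In a model adjusted for the T0 count, the bias would be b × d, where b is the slope on baseline. The article does not name the T0 count as a covariate.

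**Step 3: the scale, from the plan's own inputs.** *Sample size* gives group means from 14.9 to 23.7, f = 0.3, alpha 0.017, power 0.8 and 48 per arm.

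- Check of the plan's figure: a three-group one-way ANOVA (noncentral F) with these inputs gives 48 per arm, power 0.803. The stated 48 is reproduced.
- Range of means: 23.7 − 14.9 = 8.8.
- Implied SD = (SD of the group means) / 0.3. With the middle mean at the midpoint: 8.8 × √(1/6) / 0.3 = 12.0. With two means at one end: 8.8 × (√2/3) / 0.3 = 13.8.
- Pairwise standard error = SD × √(2/48), which is 2.44 to 2.82 episodes.

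**Step 4: illustration.** The documents give no value for d, so every row is an assumption. The type I error is for one pairwise comparison with no true effect, two-sided at 0.017, by normal approximation: Φ(−z + bias/SE) + Φ(−z − bias/SE).

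| Assumed d (episodes per 28 days) | d / 8.8 | Type I error, full shift carried | Type I error, half carried (b = 0.5, assumed) |
|---|---|---|---|
| 0 | 0% | 0.017 | 0.017 |
| 1 | 11% | 0.024 to 0.027 | 0.019 |
| 2 | 23% | 0.048 to 0.059 | 0.024 to 0.027 |
| 3 | 34% | 0.093 to 0.123 | 0.034 to 0.039 |

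The ranges reflect the two implied SDs. Adjustment with b below 1 would reduce the bias but not remove it.

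**The case against.** The strongest reply is that the bias needs participants to know their arm at T0, and the article never says that they do. Allocation is revealed to the researcher. The statement that blinding is impossible rests on the visible difference between the arms and does not fix when disclosure happens. If the researcher holds the allocation until T0 is submitted, this reporting bias does not arise. The individual timeline is in Fig. 1, which is not available here and might settle the order. Table 2 is also imperfect evidence, because its footnote labels two different time points T3. Finally, the Discussion already concedes a high risk of bias from unblinded participants.

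The point about disclosure stands and limits the conclusion to an open risk. The rest does not remove it. The table states an order that no visible text contradicts, and the general concession about blinding does not address the baseline.

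A reader might infer more than the documents support:

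- *That all baseline covariates are exposed.* Age has no plausible route to a shift, and length of illness has little. Illness severity could be affected if it is taken at T0, but its measure is not defined.
- *That loss before T0 would be highest on the waitlist.* Nothing in the article shows this, and waitlisted participants are promised the program after ten weeks.
- *That early leavers are ignored.* The plan provides for intention to treat, multiple imputation and sensitivity analysis. These address missingness but do not recover a baseline that was never collected.

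**Conclusion.** The concern holds as an avoidable risk in the stated sequence. Table 2 places the first EDE-Q after allocation, and no visible safeguard keeps the arm from participants until T0 is in. The size is unknown: the bias in an unadjusted change contrast equals the differential T0 shift, whatever that is. The 1 to 3 episode rows only show the scale. They assume that participants know their arm, that one arm shifts, that T1 reporting is unaffected, and that the SD is the one implied by f = 0.3. They are not evidence that a shift occurred.

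Either reading calls for action. If the arm is in practice withheld until T0, the published schedule misdescribes the trial. If it is not, the primary change score rests on an unprotected baseline.

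**What to change.** 1. Require the full T0 battery to be submitted online before the researcher calls the randomisation service. At minimum, require it before the participant is told the arm, and state that rule.
2. Correct *Trial design and setting* and Table 2 to read consent, T0, randomisation, access, and check that Fig. 1 agrees.
3. For participants already randomised before T0 (the study began in May 2020), record whether they knew their arm when they completed it. Add a sensitivity analysis that compares arms on the post-intervention binge count without using T0. Leave illness severity out of that model if it was measured at T0. Do not exclude these participants: if Table 2 reflects practice, exclusion could leave few or none.

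The cost is small. Items 1 and 2 re-order steps that already exist, with no new assessment and no change to the 48 per arm. With T0 completed before the arm is known, the arm-related baseline shift is zero by design. Item 3 needs one extra recorded field and one extra analysis, which may be less precise than one using a sound baseline. It removes the T0 problem only; the T1 count is still an unblinded self-report.
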